### Randomization

Randomization numbers will be provided by an independent statistician using permuted block randomization approach. Eligible patients will be randomly allocated to the intervention or the control groups in a ratio of 1:1 using computer-generated random numbers [STATA software, version 16 (Stata Corp, College Station, TX, USA] and block size six.

### Allocation concealment

Randomization codes will be provided in sealed and opaque envelopes by an independent statistician and will be opened sequentially upon patients’ admission. Randomization codes will be six-digit numbers without specified order and only one person outside the study will be aware of the identity of the codes. The Royal jelly and placebo packages are also coded using six-digit numbers according to the randomization numbers by the manufacturer.

### Blinding

The present study will be triple-blind. Royal jelly and placebo are completely identical to be not recognizable to either participants or researchers. Therefore, none of the patients are aware of the allocated treatment and will not be informed until the end of the study. Also, the researcher evaluating the outcomes is unaware of the random allocation process and the type of treatment performed. A statistician who is unaware of the randomization processes will analyze the data.

### The intervention of the experimental and the control groups

Patients who meet our eligibility criteria will be assigned to the intervention or the control groups to receive the allocated intervention for 12 weeks (Fig. 1). Individuals of the intervention group will consume 1000 mg of Royal jelly dragee daily after breakfast. To increase the adherence of participants to the allocated intervention, they will receive 28 Royal jelly dragee every 4 weeks and also will be asked to return the dragee container. Also, they will receive oral and written instructions on how to consume Royal jelly. According to the manufacturer, each Royal jelly dragee contains 820 mg of carbohydrate, 80 mg of protein, 80 mg of lipids, 3.15–3.20% of moisture, and a pH of 4.60. Each dragee contains 30% of Royal jelly powder (21 mg of 10-HDA, which corresponds to 1000 mg of fresh Royal jelly), 53% of honey powder, and 17% of filler including magnesium stearate, dicalcium phosphate, and corn starch. Honey was mixed with Royal jelly to control the taste and smell of Royal jelly and increase its compliance. The placebo dragee contains 53% honey powder and 47% of filler including magnesium stearate, dicalcium phosphate, and corn starch. Both the Royal jelly and placebo are identical in terms of size, color, shape, and flavor to make sure that they cannot be distinguished. Both the Royal jelly and placebo are produced by Kooze-asal Arya Ravis knowledge-based company, in Isfahan, Iran. Participants will be asked not to change their physical activity or diet or consume other products containing Royal jelly during the study. Moreover, they will be contacted by the investigator ([name]) every week through text messaging and phone calls.

**Fig. 1 Fig1:**
[figure not shown]
Diagram of the study process

### Baseline assessment

Eligible patients will be interviewed by a neurologist ([name]) and a nutritionist ([name]) to collect related information and complete questionnaires. Through a face-to-face interview, demographic variables of participants including age, sex, education, job, smoking, drug abuse, history of stroke in first-degree relatives, dysphagia, dysphasia, time since stroke, the affected area, co-existing disease, and medication will be gathered.

The NIHSS will be calculated for each participant at the baseline to evaluate the severity of ischemic stroke. The NIHSS is a reproducible, reliable, and valid instrument that examines 11 items including the level of consciousness, gaze, visual fields, facial palsy, motor arm and leg, ataxia, sensory, language, dysarthria, and extinction/inattention for a total score of 0–42 [23]. The score of 1–4, 5–15, 16–20, and 21–42 expressed mild, moderate, moderate to severe, and severe stroke, respectively [24].

### Outcomes

#### Severity of stroke

The severity of ischemic stroke will be evaluated by a neurologist ([name]) at baseline and post-intervention using a modified Rankin Scale (mRS). It evaluates the degree of disability or dependence in the daily activities of individuals with stroke as follows: 0 (no symptoms), 1 (no significant disability; able to carry out all usual activities, despite some symptoms), 2 (slight disability; able to look after own affairs without assistance, but unable to carry out all previous activities), 3 (moderate disability; requires some help, but able to walk unassisted), 4 (moderate to severe disability; unable to attend to own bodily needs without assistance, and unable to walk unassisted), 5 (severe disability; requires constant nursing care and attention, bedridden, incontinent), and 6 (dead) [25].

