## Background

### Background and rationale

Stroke is a debilitating disease that affects over 15 million people worldwide each year, resulting in the death of one-third of those people and severe disability in two-thirds of survivors. A stroke is a clinical syndrome that is defined as a sudden loss of focal or general brain function for more than 24 hours that can lead to death [1]. Nearly, 80% of strokes are ischemic. The incidence of stroke in men is 33% higher than in women, while the severity and rate of mortality and disability following stroke are higher in women than men [2].

One of the changes that occur at the cellular level is an increase in the inflammatory status. Inflammation of neurons following stroke is directly involved in the repair of damaged neurons and other pathologies of the disease [3]. Inflammation causes exacerbation of vascular dysfunction as well as the death of nerve cells, so the extent of inflammation is a key indicator in determining the prognosis in these patients, and controlling the inflammatory status after stroke is important in reducing secondary brain injuries [4]. Following an ischemic stroke, blood flow to certain parts of the brain is reduced, which in turn leads to a decrease in oxygen and glucose uptake by the brain cells [4]. Disruption of blood flow leads to the onset of inflammatory pathways and ultimately leads to the loss of cell antioxidant defenses and overproduction of reactive oxygen species (ROS). The resulting oxidative stress leads to neuronal dysfunction and death [5, 6]. It also plays an important role in the pathology of depression, mood disorders, cognitive function, and post-stroke fatigue [7–9]. The principal problem is a lack of specific pharmacological therapy for the wide range of post-stroke complications, while many attempts have been carried out so far [10]. Therefore, finding novel, safe, and inexpensive complementary therapies that encompass most of the post-stroke complications should be prioritized to manage this condition.

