### Sample size

The sample size was calculated based on the primary outcome of the trial, the mRS. It was assumed that a total sample of 32 patients (32 patients per group), which includes a 10% dropout factor would provide 80% power to detect a difference in the mean of mRS between the royal jelly supplementation and placebo groups. Assuming means of 1.5 in the royal jelly supplementation group and 2.1 in the placebo group; a similar standard deviation (SD) of 0.8 between the two groups; and a two-sided test with a type I error of 0.05.

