### Statistical methods

#### Statistical analysis for primary and secondary outcomes

All statistical analyses will be performed by Stata 17 (Stata Corp, College Station, TX, USA), according to the intention-to-treat (ITT) approach. We will use multiple imputations based on chained equations, which fill in missing values in multiple variables iteratively using a sequence of univariate imputation models with a fully conditional specification of prediction equations. Baseline characteristics and clinical features will be described by mean ± SD and absolute frequency (percentages) and compared between two intervention groups using the independent sample t-test for continuous data and a chi-square test for categorical data. Before statistical comparisons, all data were checked visually by a normal quantile-quantile plot (Q-Q plot) in combination with the Kolmogorov-Smirnov test for additional verification. Linear mixed-effects models will be fitted to assess changes from baseline within the treatment groups and differences of those changes between the groups concerning continuous outcomes over time. The magnitude of the effect will be presented as an adjusted mean difference and its 95% confidence interval. Also, a log-binomial regression model using robust standard error will be used to evaluate the risk of categorical outcomes between two intervention groups. The magnitude of the effect will be presented as an adjusted risk ratio (RR) and its 95% confidence interval. The independent variables included in the model are the treatment group and all potential confounders. Significance is defined as *P* < 0.01.

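### The protocol gives conflicting rules for how a death enters the primary mRS (scored 6, excluded or imputed), and does not say which version its planning SD of 0.8 describes

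*Protocol article*

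**What the plan says.** Four parts of the protocol article bear on this point.

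- **Sample size** names the endpoint: "The sample size was calculated based on the primary outcome of the trial, the mRS". It compares means: "Assuming means of 1.5 in the royal jelly supplementation group and 2.1 in the placebo group", with "a similar standard deviation (SD) of 0.8 between the two groups" and "a two-sided test with a type I error of 0.05". The result is "a total sample of 32 patients (32 patients per group), which includes a 10% dropout factor would provide 80% power". It does not say whether the SD covers survivors only or the whole scale.
- **Outcomes, Severity of stroke** defines the mRS from 0 upward and ends with "severe disability; requires constant nursing care and attention, bedridden, incontinent), and 6 (dead". Death is therefore a level of the primary outcome.
- **Eligibility criteria** lists death, together with stroke recurrence, among the exclusion criteria. An enrolled patient can meet that criterion only after entering the trial.
- **Statistical methods** commits to intention-to-treat analysis and to chained-equation imputation that will "fill in missing values in multiple variables iteratively". It says nothing separate about patients who have died.

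**The concern.** Read together, these sections allow three treatments of the same patient. A death can be scored 6 (Outcomes), removed (Eligibility criteria), or, if its mRS is regarded as missing, given a value modelled on the other patients (Statistical methods). The primary results would differ.

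The second and third treatments are the harmful ones. Death is the worst level of the primary scale, so dropping patients because they reached it is selection on the outcome. Replacing their score with a survivor-type value has much the same effect. Either way, an excess of deaths in one arm would largely vanish from the primary comparison.

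There is a knock-on question for the sample size. An SD of 0.8 is narrow for a scale on which some patients may score 6, so the reader cannot tell which version of the endpoint the power statement belongs to.

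**Working it through.** **Inputs from the Sample size section:** means 1.5 (royal jelly) and 2.1 (placebo), difference 0.6, SD 0.8, two-sided alpha 0.05, power 80%, dropout 10%. I read the size as 32 per group: that is the reading that reproduces, while 16 per group would give about 56% power. **Not in the document:** expected 12-week mortality. It is called p below and varied.

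**1. The plan's own figure.** n per arm = 2 × (1.960 + 0.842)² × 0.8² / 0.6² ≈ 27.9, so 28. With 10% dropout, 28 / 0.9 = 31.1, so 32. Power at 28 per arm is 80.1% by the normal approximation (78.7% by the exact t-test, which needs 29). The stated figure reproduces.

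**2. What a few deaths do to the estimate.** Start from -0.60 with 32 per arm and replace a patient at the arm mean by a score of 6.

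- One extra royal jelly death: the arm mean rises by (6 - 1.5)/32 = 0.14, so the difference becomes -0.46.
- Three royal jelly deaths against one placebo death: 3 × 4.5/32 = 0.42 and 3.9/32 = 0.12, so the difference becomes -0.60 + 0.42 - 0.12 = -0.30.

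If those patients are removed or imputed as survivors, this shift largely disappears.

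**3. How many deaths fit the stated mean and SD.** Suppose 1.5, 2.1 and 0.8 describe whole arms on the 0-6 scale. The one-sided Chebyshev (Cantelli) bound on the share scoring 6 is SD² / (SD² + (6 - mean)²).

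- Royal jelly: 0.64 / (0.64 + 20.25) = 3.1%.
- Placebo: 0.64 / (0.64 + 15.21) = 4.0%.

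Out of 32 that is about one death per arm, and the bound is reached only if all survivors in the arm share one score. An SD of 0.8 does not rule deaths out, but it leaves very little room for them.

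**4. Power if 0.8 is instead the survivors' SD.** This is the other reading of the same inputs and must not be combined with step 3. Let survivors have means 1.5 and 2.1 and SD 0.8, with a share p in *each* arm scored 6. The difference is then 0.6 × (1 - p), and the variance in an arm with survivor mean m is (1 - p) × 0.64 + p(1 - p)(6 - m)².

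For p = 2% the variances are 0.627 + 0.397 = 1.024 and 0.627 + 0.298 = 0.925. The pooled SD is 0.987 and the difference 0.588. Power at 32 per arm is Φ(0.588 / (0.987 × √(2/32)) - 1.960) = 0.664.

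| Assumed p, both arms | Difference | Pooled SD | Power, 28 per arm | Power, 32 per arm | n per arm for 80% |
|---|---|---|---|---|---|
| 0% | 0.600 | 0.80 | 0.801 | 0.851 | 28 |
| 1% | 0.594 | 0.90 | 0.695 | 0.752 | 36 |
| 2% | 0.588 | 0.99 | 0.606 | 0.664 | 45 |
| 5% | 0.570 | 1.20 | 0.425 | 0.473 | 71 |
| 10% | 0.540 | 1.47 | 0.278 | 0.311 | 117 |

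The 32-per-arm column is the more relevant one if deaths are scored and so not lost. A t-test simulation at 32 per arm (20,000 runs per case) gave 0.842, 0.660, 0.477 and 0.324 at 0%, 2%, 5% and 10%, in line with the table. The largest SD that keeps 80% power at 32 per arm for a difference of 0.6 is 0.857.

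**5. Unequal mortality** (royal jelly against placebo, 32 per arm): 0% against 5% gives 89%, 5% against 10% gives 64%, 5% against 15% gives 77%. The no-death reference is 85%. Both the size and the direction of the change depend on the death rate in each arm.

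**The case against.** A reader might infer that the planning SD leaves deaths out and that the 80% power is therefore wrong. The document does not support that. It never says what the SD covers, the arithmetic is correct for the stated inputs, and the failure claim needs a mortality rate that is not given. If the planning values are whole-arm values, the 80% already applies to the 0-6 scale. If deaths are removed, they could be counted within the 10% dropout, and the power would then match the analysis actually done. The equal-mortality table is one scenario, and with fewer deaths on royal jelly power can exceed the plan. All of this stands, and it limits the power part to a conditional statement.

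Nor can the Background's figure, "resulting in the death of one-third of those people", supply the rate. It describes stroke worldwide, whereas this trial restricts NIHSS to 5-20 and age to 45-80 and excludes brain-stem stroke, cardiovascular disease and malignancy.

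On imputation, it is fair to say that a patient scored 6 is not missing, so the Statistical methods section does not itself say that deaths are imputed. The risk arises only if the exclusion is applied first and the score is then treated as absent. It may also be said that a journal article leaves such handling to a fuller plan. That would answer silence, but here the article itself scores death on the scale and also excludes for it.

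Finally, death is one of several post-enrolment exclusions that sit badly with ITT. It differs from the others because it is itself a value of the primary outcome.

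**Conclusion.** The conflict over how a death enters the primary mRS is in the text and should be resolved. Following the eligibility list would remove patients for reaching the worst level of the primary outcome. With about 32 per arm a single death matters: it shifts the estimated difference by 0.14 of a planned 0.60.

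The power conclusion is weaker and conditional. The 80% is not an arithmetic error, and it is not shown to fail; it is not shown to hold for the 0-6 scale. If 0.8 is the survivors' SD and mortality is equal in both arms, power at 32 per arm would be about 75%, 66% and 47% at 1%, 2% and 5% mortality. These rates are assumptions chosen to show a range. All power figures use the alpha of 0.05 from the Sample size section.

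**What to change.** Adopt one analysis definition and carry it through four sections.

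- **Outcomes:** state that any death by week 12 is scored mRS 6.
- **Eligibility criteria:** remove death from the exclusions as a reason for leaving the analysis.
- **Statistical methods:** state that deaths stay in the ITT primary analysis with the value 6, and that mRS is imputed only for patients not known to have died.
- **Sample size:** state whether the SD of 0.8 describes survivors only or the full 0-6 scale. If survivors only, say that the 80% power applies to that version, or add a sensitivity range with its mortality assumption labelled.

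The cost is wording and possibly a less favourable power statement. No extra patients or measurements are needed, since vital status at week 12 is already required to score the mRS. Recruitment was still in progress when the article was submitted; the change should be fixed before unblinding.

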#### Cognitive function

To examine the cognitive function at the baseline and after 12 weeks of intervention, the mini-mental state examination (MMSE) test will be implemented through a face-to-face interview. This is a 30-point questionnaire that includes tests of visual-spatial skills, language, memory, attention, and orientation and was previously validated among the Persian population [26]. The overall point is interpreted as normal (score of 25–30), mild cognitive impairment (score of 20–25), moderate cognitive impairment (score of 10–20), and severe cognitive impairment (score of 0–10) [27].

#### Mental health

The mental health of stroke patients will be examined at the baseline and post-intervention via a validated, 21-item version of the depression, anxiety, stress scale (DASS-21) questionnaire through a face-to-face interview [28]. Each question is scored from 0 to 3 which is indicative of “did not apply to me at all” to “applied to me very much or most of the time”. Then, the overall scores of each domain will be multiplied by 2 to re-scale the DASS-21 to the original DASS-42. The cut-off values used for the interpretation of mental health domains as normal, mild, moderate, severe, and extremely severe are: (1) 0–14, 15–18, 19–25, 26–33, ≥34 for stress, (2) 0–7, 8–9, 10–14, 15–19, ≥20 for anxiety, and (3) 0–9, 10–13, 14–20, 21–27, and ≥ 28 for depression, respectively [29].

#### Fatigue

The fatigue severity scale (FSS) questionnaire will be used to assess the fatigue status of patients at baseline and post-intervention through a face-to-face interview. This questionnaire contains 9 questions each ranging from 1 (strong disagreement) to 7 (strong agreement) with an overall score of 9–63. Patients will be interpreted further as with mild, moderate, and severe fatigue for a total point of 0–21, 22–42, and 43–63, respectively [30]. This questionnaire was validated among the Iranian population previously [31].

#### Appetite

The validated version of the simplified nutritional appetite questionnaire (SNAQ), a 4-item self-assessment nutritional screening tool that predicts weight loss, will be completed for each individual at baseline and after 12 weeks of intervention by the first investigator using a face-to-face interview [32]. Each question contains 5 options ranging from 1 to 5 points for a sum score of 4–20 [33]. An overall score < 14 predicts a 5% risk of weight loss within the next 6 months [33].

#### Quality of life

To assess the quality of life of the patients, a validated version of the stroke-specific quality of life scale (SS-QOL) will be used through an interview with the first investigator at baseline and following 12 weeks of Royal jelly consumption [34]. This is a 49-item questionnaire that contains 12 sub-classes of quality of life including energy (3 questions), family roles (3 questions), language (5 questions), mobility (6 questions), mood (5 questions), personality (3 questions), self-care (5 questions), social roles (5 questions), thinking (3 questions), upper extremity function (5 questions), vision (3 questions), and work/productivity (3 questions). Each question is scored ranging from 1 to 5 with an overall score of 49–245. Higher values indicate a better quality of life and lower values indicate poorer quality of life [35].

#### Blood pressure

Blood pressure will be measured at baseline and post-intervention by a mercury sphygmomanometer after the patient sits for 10 minutes in two stages at intervals of at least 5 minutes, and the average of two measurements will be considered as the final blood pressure. Before taking blood pressure, patients will be asked about smoking or coffee consumption 2 hours in advance [36].

#### Mid-upper arm circumference (MUAC)

MUAC will be measured at baseline and post-intervention via a flexible non-stretchable tape to the nearest 0.1 cm by laying it to the midpoint between the olecranon processes of the ulna and acromion on the shoulder blade. It represents the average amounts of muscle and subcutaneous fat in the upper arm [37].

#### Dietary intake

The dietary intakes of individuals throughout the study will be assessed using a dietary record approach. Patients will be instructed to fill out 3-day food record sheets (2 weekdays and 1 weekend) at baseline, 6, and 12 weeks while they consume foods to diminish reliance on memory. As such a total of 9 food records will be gathered and summed up to estimate the average dietary intake during the study. Collected data will be analyzed using the nutritionist 4 software (First Databank, Hearst Corp, San Bruno, CA, USA), which was modified for Iranian foods.

#### Biochemical measures

After 12 hours of fasting, venous blood samples will be taken from the patients and centrifuged at 3500 rpm and finally, the isolated serum will be frozen at − 80 °C. All biochemical parameters will be measured in the fasting state at the beginning and end of the study. Total antioxidant capacity (TAC) will be assessed using the CUPric Reducing Antioxidant Capacity, total oxidative status (TOS) using the modified Ferrous Oxidation-xylenol Orange, Malondialdehyde (MDA) using the Thiobarbituric acid reactive substance, and nitric oxide (NO) using the Griess method according to the manufacturer’s instruction (Kiazist Life Sciences, Iran). Superoxide dismutase (SOD) will be measured based on the ability of Mn-SOD to inhibit the conversion of resazurin to resorufin via commercial kits (Kiazist Life Sciences, Iran). Glutathione Peroxidase (GPx) activity will be measured based on the reduction of hydrogen peroxide to water using commercial kits (Kiazist Life Sciences, Iran). C-reactive protein will be measured using an immunoturbidimetric approach via commercial kits (biorexfars, Shiraz, Iran). Erythrocyte sedimentation rate (ESR) will be assessed using non-hemolyzed EDTA-anticoagulated whole blood following the Westergren method (ESR analyzer, Sedimex; Parsian Teb Zaman co, Tehran, Iran) [38]. Serum levels of brain-derived neurotrophic factor (BDNF) will be measured using the ELISA method (ZelBio kit, Germany). The serum concentration of total cholesterol (TC), triglyceride (TG), and low-density lipoprotein cholesterol (LDL-C) will be measured using the enzymatic colorimetric method, and high-density lipoprotein cholesterol (HDL-C) using the photometric method via available commercial kits (biorexfars, Shiraz, Iran). Serum levels of fasting plasma glucose (FPG) will be measured using an enzymatic colorimetric method based on the activity of the glucose oxidase enzyme (biorexfars, Shiraz, Iran). Serum levels of uric acid (UA) will be examined using a TOOS approach based on UA reaction by uricase via a commercial kit (biorexfars, Shiraz, Iran). All analyses will be carried out in the clinical laboratory of Alzahra hospital.

